### Participants and procedures

#### Eligibility criteria

Clusters: Departments as clusters were included, when 1) a neuro-oncological outpatient service was present with 2) regular weekly consultation hours and 3) conducted by neurologists or neurosurgeons.Patients: We include patients with a HGG (glioblastoma WHO°IV, anaplastic astrocytoma WHO°III, anaplastic oligodendroglioma WHO°III) aged 18 years and older with the ability to give informed consent. Patient exclusion criteria are absence of written informed consent and inability to understand the German language.

#### Screening and informed consent procedure

The study coordinator or research assistant of every study center will screen the patients scheduled in the outpatient department to assess their eligibility. Then the study nurse will give each eligible patient a brief overview of the study and ask whether or not he or she would be interested in participation. The consent to participate in the study goes along with signing the consent form. In addition to the patient information, each patient receives a copy of the consent form. From decliners of the study, gender, tumor diagnosis, age, and the reason for decline will be documented (Fig. 3).

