## Methods/design

### Study design

The study is a cluster-randomized, controlled, non-blinded, multicenter study with two parallel groups to be compared (Fig. 1). The study investigates the effects of two different ways of assessing psychosocial distress in outpatient HGG patients.

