#### Setting

Patients with HGG will be recruited from 13 geographically dispersed neuro-oncological centers throughout Germany (Tübingen, Mainz, Frankfurt, Ludwigsburg, Würzburg, München, Stuttgart, Köln, Düsseldorf, Berlin, Ulm, Trier, Leipzig). The time course is displayed in Fig. 2.

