#### Randomization

The allocation to the two study arms is randomized. Through cluster randomization, the study is easier to implement into clinical routine compared to individual patient randomization. An external statistician who is not involved in treatment, planning, or evaluation of the study performed the randomization (Center for Clinical Studies in Mainz, Germany).

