#### Statistical analysis

The analysis of the primary outcome “proportion of adequate care for patients with increased psychosocial stress” will be based on hierarchical models for cluster-randomized studies (with random intercept for the clinics).

Due to the limited number of clinics, the following variables will also be adjusted: sex, age, ECOG stage, initial or recurrent disease, neurological deficit, time since initial diagnosis, living alone vs in partnership. The analyses are performed according to intent to treat. The aim is to reduce a possible bias by selective drop-out. The secondary endpoints are also calculated using mixed models.

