### Risk factors and control procedures

The following points could be identified as possible risk factors:
The questionnaire and the questions posed by the doctors address sensitive issues, which can be stressful for both patients and doctors. In addition, there may be an increased need for care because the study could reveal possible undersupply [22].Cluster randomization is used in the study. Since the clinics are regarded as clusters, the “personnel effect” must be taken into account and have to be considered in the interpretation. On the other hand—and this is of considerable importance for achieving the planned recruitment targets—cluster randomization is intended to reduce a possible hesitant recruitment of patients. Cluster randomization reduces the effort, since there is no need to act, document, and evaluate according to two different protocols (arm A, arm B) in a single center. In addition, patients with single randomization sometimes have concerns about participating in a study, which is reduced by this type of randomization [23]. Recruitment problems often arise because patients are sometimes more hesitant to participate in randomized trials. In this study, patients do not need to be told that they will be randomized if they participate in the study, as there is only one active study arm within a clinic. Furthermore, the planning of an early intermediate meeting 3 months after the start of the study serves to identify and solve problems.Since patients from all disease stages of a HGG (initial diagnosis, follow-up, and recurrent disease) are included, a survival bias may be the consequence. However, the authors point out that the questions were developed for this patient population (including all three stages) and that there were no differences in the content of relevant topics in the subpopulations leading to results transferable to clinical reality.The study protocol, standardized instruments, and the use of SOPs, as well as the consistent use of study personnel and targeted training of study personnel, reduce information and interviewer bias; on the other hand, the personnel effect is strengthened by this.Informed consent is of course required, probably leading to a selection bias: patients who decline to be in the study are not interviewed/recorded and are therefore not evaluated. Due to the few inclusion criteria and the “single-arm structure” of the study per center, the barriers to participate may be limited. This allows patients to participate in the study who often do not meet the inclusion criteria, which minimizes the selection bias. Patients who still reject are anonymously documented in order to clearly represent the selection bias.

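### Hospitals are randomized before patients are recruited by local staff, but the primary model omits the t1 distress score and the decliner log omits functional status, so selection is only partly corrected and partly visible

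*Protocol article*

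**What the plan says.** **Design and order of events.** Study design states: "The study is a cluster-randomized, controlled, non-blinded, multicenter study with two parallel groups to be compared". Randomization is reported as done ("An external statistician who is not involved in treatment, planning, or evaluation of the study performed the randomization"), while recruitment is still to come ("Patients with HGG will be recruited from 13 geographically dispersed neuro-oncological centers throughout Germany"). The section on risk factors adds that each clinic runs a single arm.

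**Who recruits.** The section on screening and consent says: "The study coordinator or research assistant of every study center will screen the patients scheduled". This takes place at the center's own clinic and serves to check eligibility. A study nurse then introduces the study to every eligible patient and asks about interest.

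**Safeguard against selection.** The same section states: "From decliners of the study, gender, tumor diagnosis, age, and the reason for decline will be documented". Risk factors and control procedures accepts that consent may cause selection bias and relies on this log: "Patients who still reject are anonymously documented in order to clearly represent the selection bias".

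**Primary model.** Statistical analysis specifies a hierarchical model with a random clinic intercept and fixes the covariates as "sex, age, ECOG stage, initial or recurrent disease, neurological deficit, time since initial diagnosis, living alone vs in partnership".

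**What t1 provides.** According to the instruments section and Table 1, patients in both arms complete the EORTC QLQ-C30 before the consultation. Table 1 lists its emotional functioning scale as the measure of emotional functioning and distress at t1 and t3. The t1 questionnaire also asks about current use of psychosocial support. The Distress Thermometer (DT) is completed in the control arm only.

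**The concern.** Randomizing hospitals balances hospital features in expectation. It does not balance who enters the study within a hospital once the arm is known. If recruiters present the study differently, or patients respond differently, because of what their hospital does, the two groups can differ before any intervention takes place.

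The primary endpoint is receipt of professional support among patients with raised distress. Severity of distress is an obvious candidate predictor of that outcome. If one arm enrols more severely distressed patients, part of the difference in receipt of care reflects case mix. The direction is not known: it could inflate a benefit or hide one. A suitable baseline measure exists in both arms, but the covariate list does not use it.

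The log has a matching gap. The Background and Preliminary work sections argue that questionnaires lose patients with neurocognitive deficits or in reduced clinical condition. The log meant to show selection bias records neither clinical condition nor neurological deficit.

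**Working it through.** **1. The plan's own figure.** Inputs from the Sample size section: 15% vs 25%, α 0.05 (taken as two-sided), power 80%, ICC 0.005, 50 patients per clinic.

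- Per arm before clustering: (1.960 + 0.842)² × (0.15 × 0.85 + 0.25 × 0.75) / 0.10² = 7.849 × 0.315 / 0.01 = 247.24.
- Design effect: 1 + (50 − 1) × 0.005 = 1.245.
- Per arm: 247.24 × 1.245 = 307.8, rounded up to 308. Total 616, as stated.

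This point does not dispute that figure, and the proposed changes do not alter it.

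**2. What is adjusted for and what can be seen.**

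| Feature | Recorded in participants | In primary model | Recorded in decliners |
|---|---|---|---|
| Age, sex | yes | yes | yes |
| Tumor diagnosis | yes (eligibility) | no | yes |
| ECOG | yes | yes | no |
| KPS | yes | no | no |
| Neurological deficit | yes (NANO) | yes | no |
| Initial/recurrent disease, time since diagnosis | yes | yes | no |
| Emotional functioning at t1 | yes, both arms | no | no |
| Use of support at t1 | yes, both arms | no | no |

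Two gaps remain. Baseline distress is measured but not used in the model. Function is used in the model but unknown for decliners.

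**3. Possible size of the bias.** The documents give no figures for this, so the following inputs are assumptions:

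- There is no true effect, and 15% receive care in both arms at equal severity.
- Severity X among patients counted in the endpoint is normal with SD 1.
- The odds ratio for care is OR per SD, with b = ln(OR).
- One arm is shifted by d SD.
- Effective size per arm is 308 / 1.245 = 247.4, so all 308 are counted, as in the plan's calculation.

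The intercept a solves E[expit(a + bX)] = 0.15. The rate in the shifted arm is q = E[expit(a + b(X + d))], and the false difference is q − 0.15. Its standard error is √(2p̄(1 − p̄)/247.4), with p̄ = (q + 0.15)/2.

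| OR per SD | Shift d | False difference (points) | Two-sided type I error |
|---|---|---|---|
| 1.2 | 0.2 | 0.47 | 5.2% |
| 1.2 | 0.5 | 1.19 | 6.5% |
| 1.5 | 0.2 | 1.04 | 6.2% |
| 1.5 | 0.5 | 2.71 | 12.9% |
| 2.0 | 0.2 | 1.74 | 8.3% |
| 2.0 | 0.5 | 4.62 | 27.4% |

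*Hand check.* To first order the difference is 0.15 × 0.85 × b × d. For OR 1.5 and d = 0.2: 0.1275 × 0.405 × 0.2 = 1.03 points, against 1.04. For OR 2.0 and d = 0.5: 0.1275 × 0.693 × 0.5 = 4.4 points, against 4.62.

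*Type I error in the last row.* p̄ = 0.173 and SE = √(2 × 0.173 × 0.827/247.4) = 0.034, so the shift is 0.0462/0.034 = 1.36 standard errors. This gives 27%.

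These figures ignore the listed covariates. To the extent that ECOG, neurological deficit and the rest carry the severity shift, the remaining bias is smaller.

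**The case against.** **Much of the risk is already addressed.** A reader might infer that differential selection is wholly uncorrected and cannot be detected. The documents do not support that. ECOG, neurological deficit, disease stage and time since diagnosis are in the model, so selection on impairment is adjusted for among participants. Table 1 plans participation rate by arm as an outcome. Decliners' age, sex, diagnosis and reasons can be compared between arms, as can participants' ECOG, KPS, NANO and t1 scores. This stands. The remaining gaps are distress in the model and function among decliners.

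**Recruiters' knowledge of the arm is inferred.** No sentence states it. It follows from an unblinded design, one arm per clinic, and a randomization reported as done while recruitment lies ahead. No masked identification is described. The inference is fair, but it remains an inference.

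**Selective approach is not planned.** The text already has every eligible scheduled patient invited. This stands. The exposure lies more in how the study is presented and who agrees.

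**The arms ask nearly the same of patients.** Both complete the QLQ-C30, BN20 and support questionnaire and have a diagnostic interview. The DT adds only minutes in the control arm. This argues against large shifts, but does not exclude moderate ones.

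**Larger bias figures need an unsuitable mix.** One might take uptake of 40% in more distressed patients and 10% in others, so that a 10-point shift in mix gives 0.10 × 0.30 = 3 points. If the others are not distressed, they are outside the endpoint's denominator. Matching the planned 15% also requires 0.10 + 0.30x = 0.15, so x is about 17%, and a 10-point shift would be a 60% relative change in mix. Nothing in the documents supports that. The calculation above uses a severity gradient within the endpoint population instead.

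**A self-reported covariate will be missing most in impaired patients.** This is true on the protocol's own premise. It calls for a missing-data rule, and is not a reason to leave the score out.

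**Conclusion.** The point holds in limited form. Patients are recruited after allocation by local staff who can be expected to know the arm, so case mix may differ between arms. The primary model corrects for selection on clinical condition but only indirectly, and so partly, for selection on distress, although a pre-consultation score exists in both arms. The decliner log cannot show whether the arms lost patients of different function, so it does not fully represent the selection bias as the protocol says it will.

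The size is unknown. Under the assumptions shown, the false difference runs from about 0.5 to 4.6 points, with type I error from about 5% to 27%. At OR 1.2 per SD it stays at or below 1.2 points. Against a planned effect of 10 points, that ranges from negligible to nearly half. The documents do not show that such a shift will occur, and they do not support calling the trial's comparison invalid. The change is worth making because it is cheap and uses data already planned.

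**What to change.** **In Statistical analysis:** add the t1 EORTC QLQ-C30 emotional functioning score to the covariates of the primary model. State that missing t1 scales will be imputed, so that impaired patients are not dropped. The DT cannot serve here because only controls complete it. Use of support at t1 is an optional further candidate, also already collected.

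**In Screening and informed consent procedure:** where consent and ethics rules allow, add clinician-rated ECOG or KPS to the anonymous decliner record, and compare it by arm together with the numbers eligible, invited and consenting. In Risk factors and control procedures, say that the log shows part of the selection bias.

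**Cost.** The covariate needs no new data collection. At the planned rates about 0.15 × 308 + 0.25 × 308 = 123 patients receive care, which can carry an eighth covariate. The price is an imputation step, likely to matter most for the most impaired patients. The log gains one field. Because Ethics approval ties data assessment to written consent, check whether the existing anonymous documentation of decliners can be extended. If it cannot, the covariate change still stands on its own. Neither change removes selection on features that nobody measures.

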**Fig. 3 Fig3:**
[figure not shown]
Recruitment procedure and flow of participants through the study. *DT* Distress Thermometer, *SCID* Structured Clinical Interview for DSM (Diagnostic and Statistical Manual of Mental Disorders)

#### Clinical information assessed in the study

The following information is documented in both arms: location of the tumor, clinical condition defined by Eastern Co-operative of Oncology Group (ECOG) status and Karnofsky Performance Score (KPS), stage of disease (initial diagnosis/recurrence), neurological deficit defined by Neurologic Assessment in Neuro-Oncology (NANO) scale [16], time since initial diagnosis, age, and gender. Furthermore, patients will provide demographic information such as professional and financial situation, family status, and current care situation.

#### Conditions of the intervention arm

Psychosocial distress is measured by three questions that emerged as important in a preliminary study. The three questions are:
Has your mood worsened due to the disease?Do physical changes due to the disease, such as numbness, weakness, or feeling exhausted more quickly, put a strain on you?Has your mental capacity worsened as a result of the disease, making it harder for you to concentrate or remember things, for example?

On the basis of the patient’s answers, the doctor offers psychosocial care, if indicated and desired by the patient, and refers the patient to the appropriate specialist services, e.g., psycho-oncological service, clinic social service, outpatient cancer counseling centers, physiotherapy, established psychotherapists, etc.

#### Conditions of the control arm

In the control arm, psychosocial distress is assessed using the DT, which can be evaluated within a few minutes, so that the results in the control group can also be discussed during the doctor–patient consultation. If there is an obvious need for treatment or if a patient requires psychosocial support, the referral is carried out analogously to the intervention condition.

#### Psychosocial care in both arms

Depending on the urgency, care must be provided quickly in both arms, i.e., within a few days to a maximum of 2 weeks, depending on the capacity of the respective cooperating services (psycho-oncological, social-legal, etc.).

### Instruments applied in the study

#### Before the doctor–patient consultation, t1

First patients complete a baseline questionnaire (t1) assessing use of and wish for psychosocial support using an adapted version of a self-developed questionnaire [17]. Further, the European Organization of Research and Treatment of Cancer Core Questionnaire (EORTC QLQ-C30) with its brain module (BN20) will be applied. It is a self-assessment tool to evaluate cancer patients’ quality of life. Validity and reliability have been previously tested in several clinical studies [18].

Patients in the control group complete additionally the DT. This is a self-reporting screening instrument, measuring psychosocial distress by a numerical rating scale accompanied by a 40-item list with problems from different areas of life, e.g., practical, family, emotional problems, etc. [5, 19].

Afterwards, the patients have the doctor–patient consultation. In the intervention group, the three questions, described above, are asked during doctor–patient consultation instead of using the DT (Table 1).

**Table 1 Tab1:** Operationalization of the outcomes and measurement points shown by outcomes

Outcome	Measure	t1	t2	t3
*Primary outcome: Psychosocial care through specialized services*				
Inpatient psycho-oncological service	Operation and procedure codes in the clinic information system or self-developed questionnaire			x
Cancer Counseling Center	Self-developed questionnaire			x
Inpatient social service	Operation and procedure codes in the clinic information system or self-developed questionnaire			x
Outpatient psychotherapy	Self-developed questionnaire			x
Neuropsychology	Medical records or operation and procedure codes in the clinic information system			x
Rehabilitation	Self-developed questionnaire or data derived from medical records			x
*Secondary outcomes*				
Percentage of patients that can be assessed for psychosocial distress	Participation rate in intervention arm vs control arm		x	
Length of doctor–patient consultation	In minutes (documentation by clinicians in the study worksheet)		x	
Emotional functioning/distress	EORTC QLQ-C30, emotional functioning scale	x		x
Health-related quality of life	EORTC QLQ-C30, global scale and BN20, all scales	x		x
Support requested	Self-developed questionnaire	x	x	x
Appointments arranged in specialized services	Documentation by clinicians in the study worksheet		x	
Direct costs of support	Calculated on the basis of the patient–doctor consultation duration			x
Accuracy of the screening method	Comparison of the screening results regarding unmet needs (intervention vs control arm) with a detailed diagnosis based on SCID interview		x	
*Evaluation of protocol adherence*	Questions to patients: whether they have completed a DT (control arm) or whether the doctor has inquired about their psychosocial condition (intervention arm)		x	

*Abbreviations*: *EORTC QLQ-C30* European Organization of Research and Treatment of Cancer Quality of Life Core Questionnaire, BN20: brain-cancer-specific module, *SCID* Structured Clinical Interview for DSM, *DT* Distress Thermometer

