### Primary and secondary endpoints

The primary endpoint is the proportion of patients with increased psychosocial stress who receive professional support from psychosocial services (psycho-oncology, social services, cancer counseling centers, palliative care with psychosocial support).

Secondary endpoints are number of patients reporting psychosocial stress; number of patients receiving psychosocial care through specialized services such as psycho-oncology, social services, cancer counseling centers, palliative care, etc.; number of patients referred to care structures; quality of life; need for support; psychological well-being and burden of the patients before and after doctor–patient consultation; and duration of the doctor–patient consultation.

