#### Follow-up, t3

Three months later, the patients will complete the EORTC QLQ-C30 + BN20 questionnaire and again an adapted version of the self-developed questionnaire (Table 1) in order to assess the proportion of patients receiving adequate care.

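### Neuropsychology is the only primary-outcome service in Table 1 without the patient questionnaire as a source, so care received outside the recruiting hospital is not systematically captured

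*Protocol article*

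**What the plan says.** Table 1 has six service rows under the primary outcome, all measured at t3. Their listed sources are:

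- Inpatient psycho-oncological service and inpatient social service: "Operation and procedure codes in the clinic information system or self-developed questionnaire".
- Cancer counseling center and outpatient psychotherapy: the "self-developed questionnaire" alone.
- Rehabilitation: "Self-developed questionnaire or data derived from medical records".
- Neuropsychology: "Medical records or operation and procedure codes in the clinic information system".

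The Follow-up, t3 section gives the adapted self-developed questionnaire to patients at three months "in order to assess the proportion of patients receiving adequate care".

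Under Conditions of the intervention arm, the third of the three questions is "Has your mental capacity worsened as a result of the disease, making it harder for you to concentrate or remember things, for example". The same section foresees referral beyond the hospital; its examples of target services include "outpatient cancer counseling centers, physiotherapy, established psychotherapists, etc". Neuropsychology is not among the examples. Conditions of the control arm says that referral works in the same way there.

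Primary and secondary endpoints defines the counted services as "psycho-oncology, social services, cancer counseling centers, palliative care with psychosocial support". That list does not name neuropsychology. It does name palliative care, which has no primary-outcome row in Table 1.

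**The concern.** The trial enrolls outpatients, and neuropsychology, unlike two other rows, is not labelled as an inpatient service. Yet it is the one row in which no listed source asks the patient. A patient who sees a neuropsychologist in private practice or at another institution within the three months is counted for that service only if a report reaches the recruiting hospital's records.

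Two things are at stake. First, ascertainment of one endpoint component varies with whether the hospital has neuropsychology in-house and whether it files outside letters. With 13 randomized hospitals, chance can leave such features unevenly spread between the arms, and they add between-hospital variation to a design that assumes an ICC of only 0.005. Second, a positive answer to the cognition question could naturally lead to neuropsychology. If so, some of the care the intervention is meant to bring about is the care most easily missed, and the observed contrast would shrink.

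**Working it through.** **Reading of Table 1.** The questionnaire is listed in five of six primary-outcome rows, alone or as an alternative. It is listed even for the two inpatient services, where hospital codes should be most complete, and for rehabilitation, where medical records are also listed. The neuropsychology row is the exception.

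**Reproducing the plan's sample size.** Inputs from the Sample size section: 15% versus 25%, α 0.05 (taken as two-sided, which is not stated), power 80%, ICC 0.005, 50 patients per clinic.

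- Per arm before clustering: (1.960 + 0.842)² × (0.15×0.85 + 0.25×0.75) / 0.10² = 247.24
- Design effect: 1 + (50 − 1) × 0.005 = 1.245
- Total: 2 × 247.24 × 1.245 = 615.6, rounded up to 616, as stated
- Effective number per arm: 308 / 1.245 = 247.4

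**Illustration of missed events.** Suppose some patients have outside neuropsychology as their only counted service and are missed. The documents give no rate for this, so the losses are assumptions. Power is Φ(d × √(247.4 / v) − 1.960), where d is the observed difference and v = p₁(1 − p₁) + p₂(1 − p₂). For example, at 15% versus 24%, v = 0.3099 and 0.09 × √(247.4 / 0.3099) = 2.543. Subtracting 1.960 leaves 0.583, and Φ(0.583) = 0.720. The last column uses the pooled variance under the null hypothesis.

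| Points missed, control / intervention | Observed rates | Power, plan's (unpooled) formula | Power, pooled |
|---|---|---|---|
| 0 / 0 | 15% vs 25% | 80.0% | 79.6% |
| 0 / 1 | 15% vs 24% | 72.0% | 71.6% |
| 0 / 2 | 15% vs 23% | 62.6% | 62.2% |
| 0 / 3 | 15% vs 22% | 52.1% | 51.8% |
| 1 / 2 | 14% vs 23% | 73.7% | 73.3% |
| 1 / 1 | 14% vs 24% | 81.6% | 81.1% |

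The two formulas differ by less than half a point. Power falls only when more points are missed in the intervention arm than in control. Equal absolute losses leave the difference at 10 points and, because the rates are lower, slightly raise power.

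Like the plan's own calculation, this treats all 616 patients as contributing to the primary comparison and holds the ICC at 0.005. It does not price any added between-hospital variation, for which the documents give no figure.

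**The case against.** Much can be said for the plan, and part of it stands.

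- **Records are not blind to outside care.** The row lists medical records as well as codes, and letters from other providers can be filed there. This stands: outside care is not systematically captured, but it would be wrong to say that it is not captured at all.
- **No difference between arms is shown.** A reader might infer that the endpoint is biased against the intervention and that power falls to 52%. The documents do not support that. The source rule is the same in both arms and referral is analogous. Control patients complete the Distress Thermometer with its 40-item problem list, and a positive cognition answer could also lead to services that do have a questionnaire source. The 52% figure is the extreme of a one-sided assumption.
- **Neuropsychology may not count.** The endpoint definition does not name it. If that list governs, the gap does not touch the primary endpoint. This stands as a reason to settle the list, but Table 1 does place neuropsychology under the primary outcome.
- **The questionnaire's items are not shown.** It may already ask about neuropsychology. That affects how much work the fix needs. It does not change the source rule in Table 1, which does not assign the questionnaire to this service.
- **Impaired patients may report poorly.** The Background makes this point, and it supports keeping records. It does not support omitting the patient's report, since the plan relies on the questionnaire alone for two other services in the same population.
- **Local conditions are documented and clinics get a random intercept.** The intercept accounts for variation between hospitals but does not recover missed events. The adjustment variables listed under Statistical analysis are all patient characteristics.

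**Conclusion.** The point holds as a weakness in how one component of the primary outcome is ascertained. As Table 1 stands, outside neuropsychological care is captured unsystematically and in a way that depends on the hospital. Dilution of the contrast is plausible because the intervention asks about cognition, but it is not demonstrated. Its size is unknown: under the assumed losses power ranges from about 52% (3 points missed, intervention arm only) to about 81% (1 point missed in each arm), against the planned 80%. These figures require that the missed care was the patient's only counted service. Calling neuropsychology the only service without a questionnaire source is true of the Table 1 rows, not of the whole article, since palliative care is in the endpoint definition and has no primary-outcome row. The correction is worth making because it is cheap and clearly improves ascertainment, not because a large loss has been established.

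**What to change.** In Table 1, change the neuropsychology measure to the t3 self-developed questionnaire plus medical records and procedure codes, with all of these sources used for all patients in both arms. Check that the t3 questionnaire has an item on neuropsychological care from any provider, and add one if it does not.

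In the same edit, reconcile the service list under Primary and secondary endpoints with Table 1: the first names palliative care and not neuropsychology, the second the reverse. State which services count toward the primary endpoint and give each one a source.

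The cost is one table cell, one aligned list and at most one item on a form that patients already complete. Patients already followed up may lack the item, so their neuropsychology data would still rest on records alone; the report should say how many there are in each arm.
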